**Randomization and randomization concealment**

A random sequence will be generated by using the online software Random Sequence Generator, which is available at URL: [www.random.org](http://www.random.org). [23] It will be done by an investigator with no clinical involvement in the trial. [name] will be responsible for enrollment of the patients. The method for randomization concealment is to use sequentially numbered, opaque, sealed envelopes (SNOSE). The envelopes are kept in a safe box, which was only accessible to [name] who will be responsible for assigning the patients to the interventions.

**Interventions**

Eligible patients will be randomly allocated into three groups and treated for 6 weeks with:

- a) weekly injections of intralesional (i.l.) MA (Glucantime®; Rhodia Laboratories, Rhone-Poulenc, France) alone,
- b) weekly injections of i.l. MA combined with application of a non-silver dressing (Atrauman® ,Hartmann, CMC Consumer Medical Care GmbH, Germany) on the lesions,
- c) weekly injections of i.l. MA combined with application of a silver containing dressing (Atrauman® Ag, Hartmann, CMC Consumer Medical Care GmbH, Germany) on the lesions.

MA will be injected by using insulin syringes with 30-G needles, 0.1 milliliter. The drug will be infiltrated intradermally in each one square centimeter of a lesion, first at the circumference and then in the center if necessary, depending on the size of each lesion until blanching occurred. The dressings will be applied on the lesions and the patients will be asked to change it every other day. Base of both dressings are similar and are made of polyester.

### **Follow up**

An assessor who is blinded to the type of treatment will visit the patients at weekly intervals during the treatment period and 1-month and 5 months after the last treatment session. The patients will receive their dressings from the members of the study team other than the assessors and will be instructed to take off their dressings before each visit and not to explain to assessors whether they have used dressing or not.

### **Documentation**

In each visit the characteristics of the lesions including the number, location, size of induration, ulcer, scar (greatest diameter multiplied by diameter perpendicular to it), adverse events, and concomitant treatment (if any) will be recorded on the Case Report Forms (CRFs).

**Sample size**

Fifty-six lesions per treatment group were needed to have 80% power to detect a significant difference in the expected cure rate of 60% in the i.l MA alone group and the desired cure rate of 85% in the i.l. MA and either silver or non-silver dressing-treated group at week 10 with a type I error level of 0.05. Compensating for a 20% loss-to-follow up, recruiting 68 (round up to 70) lesions per treatment group will be reasonable.

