## Aim and objectives

**Primary objective:** To compare the proportion of cured patients between treatment group treated with intralesional injections of meglumine antimoniate MA and non-silver dressing and treatment group treated with intralesional injections of meglumine antimoniate 10 and 14 weeks of follow-up.

To compare the proportion of cured patients between treatment group treated with intralesional injections of meglumine antimoniate and silver dressing and treatment group treated with intralesional injections of meglumine antimoniate 10 and 14 weeks of follow-up.

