## **Patients and Methods**

### **Design and setting**

This study is designed as a three parallel arm with 1:1:1 allocation ratio randomized, assessor-blind clinical trial and will be conducted in Kashan where is endemic for CL due to *L. major*.

Kashan is located about 210 km south of Tehran, capital of Iran.

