**Exclusion criteria**

- a) Pregnant or lactating women
- b) Duration of lesion more than 3 months
- c) Number of lesions more than 5
- d) Ulcer size greater than 5 cm in largest diameter
- e) History of receiving full course standard treatment (antimonials)
- f) History of allergy to meglumine antimoniate (MA) or silver
- g) Serious systemic illnesses (as judged by the physician)
- h) Participation in any drug trials in the last 60 days
- i) Indication for systemic treatment with MA
- j) Presence of secondary bacterial infection of the lesion according to clinical appearance.

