**Outcome measures**

The primary end point of this study is the clinical cure of the lesion (complete healing is defined as more than 75% reduction , clinical improvement defined as 50%-75% reduction, and no response to treatment defined as less than 50% reduction in the size of the lesion compared with baseline). The end-points will be assessed at the end of the treatment period (end of week 6) and 4 weeks later.

The secondary end-points include treatment related side effects and relapse. The relapse is defined as a reappearance of lesions at the site or periphery of previously healed lesions or an increase in the size of lesions after initial improvement was assessed 5 months after the termination of treatment.

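### Patients are randomised and the objective counts cured patients, but the endpoint and sample size count lesions with no design effect, so 80% power holds only if within-patient correlation is weak

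*Protocol*

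**What the plan says.** The protocol uses two different units.

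- **Patient.** Under Interventions, "Eligible patients will be randomly allocated into three groups". Design and setting describes a "three parallel arm with 1:1:1 allocation ratio randomized, assessor-blind clinical trial". The primary objective in Aim and objectives is "To compare the proportion of cured patients between treatment group treated with intralesional injections", and Goal and Objectives repeats it in patients.
- **Lesion.** Under Outcome measures, "The primary end point of this study is the clinical cure of the lesion". Under Sample size, "Fifty-six lesions per treatment group were needed to have 80% power to detect a significant difference", based on an "expected cure rate of 60% in the i.l MA alone group" against 85% with either dressing at week 10. The number recruited is 68, rounded up to 70 lesions per arm, to cover 20% loss.

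The two units coincide only if each patient has one lesion. The relevant exclusion criterion is "Number of lesions more than 5", so one to five are allowed. Statistical methods plans absolute risk reductions in complete healing with 95% confidence intervals, and defines healing by the size of the lesion. The protocol gives no index-lesion rule, no rule for calling a patient with several lesions cured, no patient number, no expected lesions per patient and no ICC.

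**The concern.** Lesions of one patient share the host, the allocated treatment and the patient's adherence, so their outcomes are likely to be positively correlated. Fifty-six correlated lesions then carry less information than 56 independent ones. Three things are at stake:

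- A valid analysis of the planned number of lesions may have less than the stated 80% power.
- If lesions are analysed as independent, the confidence intervals are too narrow and the test rejects too often.
- A recruitment target in lesions does not fix the number of randomised units. If the patient-or-lesion choice stays open, it could be made after the data are seen, and it changes the quantity being estimated.

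**Working it through.** **Inputs from the protocol:** cure 60% versus 85%, 80% power, 5% type I error, 56 lesions per arm, 20% loss, 70 recruited (Sample size); two-sided test (Statistical methods); at most five lesions per patient (Exclusion criteria).

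**Step 1: reproduce the 56.** With mean proportion 0.725 and difference 0.25,

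n = [1.96·√(2·0.725·0.275) + 0.842·√(0.60·0.40 + 0.85·0.15)]² / 0.25² = 48.9, or 49 per arm.

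With continuity correction,

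n′ = (48.9/4)·[1 + √(1 + 4/(48.9·0.25))]² = 56.6, or 57 when rounded up.

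The stated 56 therefore agrees with the continuity-corrected formula for independent observations to within one. It contains no design effect. The loss allowance is 56 × 1.2 = 67.2 (68), or 56/0.8 = 70.

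**Step 2: the slack.** Without continuity correction, 56 independent lesions give 85% power and 49 give 80%. The largest design effect that keeps 80% is 56/49 = 1.14. With the correction, 56 gives 79.5% and there is no slack.

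**Step 3: design effect.** DE = 1 + (m* − 1)·ICC, where m* = Σm²/Σm allows for unequal lesion counts. The protocol gives no lesion distribution, so I assume 45/25/15/10/5% of patients with 1/2/3/4/5 lesions:

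- mean = 0.45 + 0.50 + 0.45 + 0.40 + 0.25 = 2.05
- mean square = 0.45 + 1.00 + 1.35 + 1.60 + 1.25 = 5.65
- m* = 5.65/2.05 = 2.76

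The slack is used up at ICC = 0.14/1.76 = 0.08. With exactly two lesions each it is used up at 0.14, and with five each at 0.14/4 = 0.035.

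**Step 4: power and type I error at 56 lesions per arm.** The formula columns use effective n = 56/DE in the uncorrected power formula, and 2·[1 − Φ(1.96/√DE)] for the unadjusted test. The simulated columns use beta-binomial lesions with the same distribution. Power there is for a cluster-robust t test on patients, and type I error is for the unadjusted lesion-level z test with both arms at 60%.

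| ICC | DE | Power, formula | Power, simulated | Unadjusted type I error, formula | Unadjusted type I error, simulated |
|---|---|---|---|---|---|
| 0 | 1.00 | 85% | 86% | 5.0% | 4.8% |
| 0.05 | 1.09 | 82% | 82% | 6.0% | 5.3% |
| 0.1 | 1.18 | 79% | 78% | 7.1% | 6.8% |
| 0.2 | 1.35 | 73% | 75% | 9.2% | 8.7% |
| 0.3 | 1.53 | 68% | 70% | 11.3% | 11% |
| 0.5 | 1.88 | 58% | 62% | 15.3% | 15% |

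Repeated simulation runs differ by up to about 3 percentage points.

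These powers are for tests without continuity correction, so the baseline to compare them with is 85–86%, not 80%. On the continuity-corrected basis that yields 56, power is lower: with two lesions each it is 66% at ICC 0.3 (75% uncorrected) and 58% at ICC 0.5 (68% uncorrected).

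**Step 5: randomised units.** Seventy lesions per arm is 70/5 = 14 patients if all have five lesions, and 70 patients if all have one. At the assumed mean it is 70/2.05 ≈ 34.

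**The case against.** Three points on the other side carry weight.

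- **The size of the effect is assumed.** The documents give neither lesion counts nor ICC. At ICC 0.05 to 0.1 the power is about 82% to 78%, which is close to plan, and type I error is only 5.3% to 6.8%. This stands. A reader might infer that the stated 80% power simply fails; the documents do not support that. They support only that it fails once the design effect passes about 1.14.
- **The analysis may not be on lesions.** Statistical methods never names the denominator. It promises intent-to-treat and also compares withdrawal, which is a patient event under Withdrawal criteria. A clustered variance or a patient-level analysis could also sit in a statistical analysis plan that is not shown. This partly stands. A reader might infer that the 5% error rate is definitely broken, but that follows only if lesions are analysed as independent. That is the natural reading, because healing is defined by lesion size, but it is not the only one. A separate plan could restore the error rate. It could not make 56 correlated lesions as informative as 56 independent ones.
- **Lesion may be loose wording for patient.** If so, the protocol still needs a rule that turns one to five lesion outcomes into one patient outcome, and it has none. The 60% and 85% would also have to be patient-level rates, which it does not say.

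**Conclusion.** The concern holds in conditional form. The mismatch of units is certain from the text: patients are randomised and named in the primary objective, while lesions are the endpoint and the sample-size unit. It is also clear that 56 matches an independent-observations formula and contains no design effect. The consequences depend on figures the protocol does not give. With one to five lesions per patient, mean about 2, valid power at 56 lesions per arm runs from about 86% at ICC 0 to 62% at ICC 0.5, and drops below 80% at an ICC of roughly 0.08 to 0.1. Unadjusted lesion-level testing would have a type I error of about 5.3% to 15% for ICC 0.05 to 0.5. The problem disappears only with one lesion per patient or no within-patient correlation, and the protocol states neither. It affects both primary comparisons and the recruitment target, so it should be settled before analysis.

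**What to change.** Make the patient the unit of inference in Outcome measures, Sample size and Statistical methods, in one of two ways:

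- (a) Define the primary endpoint as patient-level cure, with a stated rule for combining a patient's lesions. This matches the objective. Base the sample size on patient-level cure rates.
- (b) Keep the lesion endpoint, reword the objective to match, and estimate the risk difference and its 95% confidence interval by GEE or a cluster-robust variance with patient as cluster.

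Under either, state the target in patients per arm. Restate the power with an explicit mean lesion count and, wherever lesions remain the unit, a range of ICC values.

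The cost is wording in three sections and, under (b), a different variance estimator. No new data are needed, since Documentation already has lesion number and size recorded at each visit. The real downside is that the stated power becomes less favourable at the planned size. Keeping it instead would mean more recruitment. For example, with two lesions per patient and ICC 0.3, DE = 1.3 gives 56 × 1.3 = 72.8, or 73 lesions per arm, and 72.8/0.8 = 91 after 20% loss, against 70 planned. With three lesions each, DE = 1.6 gives 90 and 112.

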**Outcome measures**

The primary end point of this study is the clinical cure of the lesion (complete healing is defined as more than 75% reduction , clinical improvement defined as 50%-75% reduction, and no response to treatment defined as less than 50% reduction in the size of the lesion compared with baseline). The end-points will be assessed at the end of the treatment period (end of week 6) and 4 weeks later.

The secondary end-points include treatment related side effects and relapse. The relapse is defined as a reappearance of lesions at the site or periphery of previously healed lesions or an increase in the size of lesions after initial improvement was assessed 5 months after the termination of treatment.

**Statistical methods**

The recorded data will be entered in SPSS 17 for Windows software (SPSS Inc, Chicago, Ill, USA). Normally distributed data will be reported as mean  $\pm$  standard deviation (SD). If the distribution of data do not follow the Normal distribution, median and interquartile range will be reported. An intent-to-treat analysis will be performed at 2 time points (end of the treatment period [day 42] and one month later [day 72]). The proportions of complete healing, clinical improvement, and withdrawal will be compared between the two groups by calculating Absolute

Risk Reductions (ARR) based on the proportion of complete healing, which is defined as more than 75% reduction in the size of the lesion compared with baseline in each group. Ninety-five percent confidence intervals (95% CIs) will be provided. To compare the mean for data with normal distribution one-way analysis of variance (ANOVA) and for data that do not follow normal distribution proper nonparametric statistical tests were used. Fisher exact test was used to compare the rates of relapse and drug-related adverse events. A 2-sided  $P < 0.05$  will be considered significant.

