## **Goal and Objectives**

Primary objective: To compare the proportion of cured patients between treatment group treated with intralesional (i.l.) injections of meglumine antimoniate (MA) (and non-silver dressing and treatment group treated with intralesional (i.l.) injections of meglumine antimoniate (MA) 10 and 14 weeks of follow-up . To compare the proportion of cured patients between treatment group treated with intralesional (i.l.) injections of meglumine antimoniate (MA) and silver dressing and treatment group treated with intralesional (i.l.) injections of meglumine antimoniate (MA) 10 and 14 weeks of follow-up.

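### Two primary dressing comparisons, each at two times, are all judged at an unadjusted 0.05 with no single primary time, while the sample size covers one comparison at week 10

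*Protocol*

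**What the plan says.** **Comparisons.** Aim and objectives, and again Goal and Objectives, put two contrasts under the primary objective: MA plus non-silver dressing versus MA, and MA plus silver dressing versus MA. Each begins "To compare the proportion of cured patients between treatment group treated with intralesional (i.l.) injections" and each is set at weeks 10 and 14.

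**Times.** Outcome measures assesses the primary end point at the end of week 6 and four weeks later. Statistical methods agrees with that and not with the objectives: "An intent-to-treat analysis will be performed at 2 time points (end of the treatment period [day 42] and one month later [day 72".

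**Decision rule.** Statistical methods gives one rule for everything: "A 2-sided $P < 0.05$ will be considered significant". There is no order of testing, no division of alpha, and no requirement that both arms or both times succeed.

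**Sample size.** "Fifty-six lesions per treatment group were needed to have 80% power", with an "expected cure rate of 60% in the i.l MA alone group" and 85% assumed for either of the dressing arms. The calculation is placed "at week 10 with a type I error level of 0.05". This is one two-group comparison at one time.

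**The concern.** The 0.05 in the sample size and in the decision rule is the error rate of one test. The primary analysis as written holds four: two arms by two times. The objectives and the outcome section also name different pairs of times, so week 6, week 10 or week 14 could each be presented as primary once the data are known.

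Both contrasts use the same MA arm. A chance low cure rate in that arm makes both dressings look effective together.

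Two things are at stake: the false-positive rate behind a claim that a dressing adds to MA, and the stated 80% power, which was computed for a single unadjusted test.

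**Working it through.** **Inputs.** From Sample size: cure 60% versus 85%, type I error 0.05, power 80%, 56 lesions per group, 20% loss. From Design and setting: three arms, 1:1:1. Assumed, because the documents give no figure: the correlation between the two times. Lesions are treated as independent, as the sample size treats them.

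**1. The stated sample size.** With mean rate 0.725 and difference 0.25:

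n = [1.96·√(2·0.725·0.275) + 0.8416·√(0.60·0.40 + 0.85·0.15)]² / 0.25² = (1.2377 + 0.5102)² / 0.0625 = 48.9, so 49.

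Continuity-corrected: (48.9/4)·[1 + √(1 + 4/(48.9·0.25))]² = 56.6, so 57.

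Exact power of the two-sided Fisher test is 79.8% at 55 and 80.8% at 56. So 56 reproduces with Fisher's test at an unadjusted 0.05. For loss, 56 × 1.2 = 67.2 gives 68, and 56/0.8 = 70.

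**2. Correlation between the arm contrasts.** With equal arms, each difference has variance 2σ²/n and the shared control gives covariance σ²/n, so the correlation is 0.5.

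**3. Familywise error with uncorrected tests.** This is P(any |Z| > 1.96) for normal statistics with correlation 0.5 between arms and r between times, by simulation.

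| Tests | Assumed r | Error |
|---|---|---|
| Two arms, one time | – | 9.1% |
| Two arms, two times | 0.8 | 13.9% |
| Two arms, two times | 0.7 | 14.8% |
| Two arms, two times | 0.5 | 16.1% |
| Two arms, two times | 1 to 0 | 9.1% to 17.3% |
| One arm, two times | 0.8 to 0.5 | about 8–9% |

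**4. Familywise error with Fisher's test.** Binary data were simulated at 56 per arm, with null cure 60% at week 10 and 40% or 60% at week 6, and an assumed latent within-lesion correlation of 0.5 to 0.8. Fisher's test is conservative at this size, so the figures are lower: about 5.6% for two arms at week 10, about 10–11% for all four tests, and about 5.5–6% for one arm at two times.

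**5. Power at 56 per arm if week 10 is the only primary time.** Holm's first step is at 0.05/2 = 0.025. If that step rejects, the other arm is tested at 0.05.

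| 60% vs 85% | Fisher | Uncorrected |
|---|---|---|
| Unadjusted 0.05 | 81% | 85% |
| Holm, only one dressing works | about 72% | 77–78% |
| Holm, per arm, both work | about 77% | about 83% |
| Holm, at least one arm positive, both work | about 85% | about 90% |

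The sample-size section assumes 85% in either dressing arm, so the last two rows match the plan's own scenario. There the per-arm loss from Holm is about 4 points with Fisher (81 to 77) or 2 to 3 uncorrected (85 to 83).

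**The case against.** **The arms may be separate questions.** The protocol asks about each dressing in turn, and the Background gives silver its own antimicrobial and anti-leishmanial rationale. Whether separate questions with a shared control need familywise control is disputed. This stands. A reader might infer that the trial succeeds if any one of four tests is positive, or that it makes a single claim that a dressing improves cure. The protocol states neither. The familywise figures therefore hold only if any positive result may support a claim. The repeated times remain a problem within each arm even so.

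**The 14–16% might be read as a property of the design.** It is not. It depends on an assumed between-time correlation and on uncorrected tests. The protocol names no test for cure; it plans absolute risk reductions with 95% confidence intervals and reserves Fisher's test for relapse and adverse events. The 80% power at 56 fits Fisher's test, so setting 14–16% error beside a fall from 80% power would mix two tests.

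**Power might be thought to fall to about 70% in each arm.** That is the first-step figure, for when only one dressing works. It does not describe Holm under the protocol's own assumption of 85% in either arm.

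**Week 10 may already be the primary time.** Sample size names only week 10, but the objectives, Outcome measures and Statistical methods do not single it out. Even on that reading the two arm contrasts give about 9% uncorrected, or 5.6% with Fisher.

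**The SAP may settle it.** Order of testing is often left there. But this protocol fixes 0.05 in two places and contradicts itself on the primary times, which a SAP cannot mend without departing from one section or another.

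**The 56 may already include a split.** An unpooled formula at 0.025 gives 55.9. This looks like coincidence: the text states 0.05 and mentions no split.

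**Conclusion.** The concern holds in a limited form. The primary analysis has two comparisons at two times, all at an unadjusted two-sided 0.05, and the sections disagree on which times. If any positive result may support a claim, the familywise error is above 5% on every assumption tried. Its size runs from about 5.6% (Fisher, two arms, week 10 only) to about 17% (uncorrected, four tests, times uncorrelated). With four uncorrected tests and a between-time correlation of 0.8 to 0.5 it is about 14–16%; with Fisher's test it is about 10–11%. If the arms are treated as separate questions, two times per arm still give about 8–9% uncorrected or 5.5–6% with Fisher.

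All of this treats lesions as independent; clustering within patients is a separate matter that these figures leave out. The point is worth correcting before analysis, but it does not undermine the design, and the cost in power is modest.

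**What to change.** 1. Name week 10, the time already used for the sample size, as the only primary time. Make Aim and objectives, Goal and Objectives, Outcome measures and Statistical methods agree on it.
2. Make week 6, week 14, clinical improvement and withdrawal secondary, with unadjusted confidence intervals. The Follow up section schedules no assessment at week 14, so that section and the objectives must also be reconciled.
3. Name the test for cure. Test the two dressing-versus-MA comparisons at week 10 with Holm (or Dunnett) at a familywise two-sided 0.05. Alternatively, state outright that they are separate questions and that 0.05 applies to each. In either case, replace the reference to comparing two groups with the two named contrasts.
4. If Holm is used, restate the power at 56 lesions per arm from the table above, for the test chosen, and say that it makes no allowance for clustering.

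The cost is edits to four or five short sections and a slightly less favourable stated power. No extra patients are needed.

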## **Secondary objectives**

### **To compare:**

- the proportion of relapsed patients 6 months after initiation of treatment
- the proportion of adverse effects during the study period in three groups

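### The only named safety test is limited to drug-related events, although the drug is common to all arms and only the dressing is randomised; objective, endpoint and test give three different scopes

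*Protocol*

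**What the plan says.** Four parts of the protocol bear on the safety comparison, and they describe its scope differently.

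- **Objective.** Secondary objectives, in both the Summary and the main text, set out to compare "the proportion of adverse effects during the study period in three groups". There is no relatedness filter.
- **Endpoint.** Outcome measures is narrower: "The secondary end-points include treatment related side effects and relapse".
- **Test.** Statistical methods is narrower again: "Fisher exact test was used to compare the rates of relapse and drug-related adverse events". No other test for adverse events is named.
- **Data.** Documentation has adverse events recorded on the case report form at each visit, again without a filter.

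Interventions defines the arms as "weekly injections of intralesional (i.l.) MA (Glucantime®; Rhodia Laboratories, Rhone-Poulenc, France) alone", "weekly injections of i.l. MA combined with application of a non-silver dressing" and "weekly injections of i.l. MA combined with application of a silver containing dressing". The MA component is the same in all three. Exclusion criteria lists "History of allergy to meglumine antimoniate (MA) or silver", so the protocol itself treats silver as a possible cause of reactions and names it separately from the drug.

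Follow up has a blinded assessor make the visits. Patients remove their dressings beforehand and do not say whether they used one. The protocol does not define the term drug-related, does not say whether a dressing counts as a drug, and does not say who judges relatedness.

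**The concern.** The randomised difference between arms is the dressing. A safety comparison in this trial should therefore be able to show whether adding a plain or a silver dressing changes the rate of adverse events. The named test is instead restricted by attribution to the one component that every arm receives. If the filter is applied as worded, a contact reaction or irritation put down to the dressing may not be counted.

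At stake is a secondary safety conclusion. A report of no difference between dressing arms and control could come from an analysis that had set aside some of the events that the dressings caused, and a reader would take it as an answer to the broader objective.

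There is also a practical difficulty. The filter needs a drug-or-dressing judgement for each event. An assessor who does not know whether a dressing was used has no sound basis for it, so what enters the test would depend on uncertain attribution.

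**Working it through.** **1. The plan's own figure.** The only computed design figure is the cure sample size, 56 lesions per group for 60% against 85%. The usual two-sided formula at 0.05 with 80% power gives

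(1.96 × √(2 × 0.725 × 0.275) + 0.8416 × √(0.60 × 0.40 + 0.85 × 0.15))² / 0.25² = 48.9,

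that is, 49. The continuity correction gives (48.9/4) × (1 + √(1 + 4/(48.9 × 0.25)))² = 56.6, so 57 against the stated 56. The figure reproduces within rounding. It concerns cure and counts lesions, and this point does not depend on it. No figure is given for safety.

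**2. The scopes side by side.**

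| Place in the protocol | Events covered | Dressing reactions included? |
|---|---|---|
| Secondary objectives | all adverse effects | yes |
| Documentation | all adverse events | yes |
| Outcome measures | treatment-related | yes, if treatment means the allocated regimen |
| Statistical methods | drug-related | not on a literal reading; undefined |

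The set narrows at each step from objective to endpoint to test. The term used last names the component shared by all arms.

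**3. Illustration of size.** All rates below are assumptions.

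- Background events: 10% of patients in every arm.
- Reactions caused by a dressing: a further d of 5%, 10%, 15% or 20% in a dressing arm, independent of the background, and none in control.
- Any-cause rate in the dressing arm: 1 − (1 − 0.10)(1 − d). For d = 15% this is 1 − 0.90 × 0.85 = 23.5%.
- Test: pairwise two-sided Fisher exact test at 0.05. Power is the sum, over all pairs of counts (a, b), of Bin(a; n, p₁) × Bin(b; n, p₂) wherever the Fisher p-value is below 0.05.
- Unit: patients. The planned 70 per group in Sample size are lesions, and Exclusion criteria allows up to five per patient, so patients may be fewer. The table shows 70 per arm (one lesion each) and 35 per arm (two lesions each, assumed).

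| d | Any-cause rates | Power, n = 70 | Power, n = 35 |
|---|---|---|---|
| 5% | 10% vs 14.5% | 8% | 4% |
| 10% | 10% vs 19% | 25% | 11% |
| 15% | 10% vs 23.5% | 50% | 23% |
| 20% | 10% vs 28% | 73% | 38% |
| any d, dressing reactions fully filtered out | 10% vs 10% | 2.5% | 1.3% |

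The last row is the extreme case, in which every dressing reaction is correctly recognised and excluded. If half of the dressing reactions were recorded as drug-related, the test would behave as in the row for half of d. For d = 20% at 70 per arm, power would be 25% instead of 73%.

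**4. What background events cost.** A comparison of dressing-caused reactions alone (0% vs d) has power of 14% at d = 5% and 96% at d = 15% with 70 per arm, and 43% at d = 15% with 35 per arm. Counting all causes shrinks the 15-point difference only to 23.5 − 10 = 13.5 points, but on these assumptions power falls from 96% to 50% at 70 per arm and from 43% to 23% at 35.

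**The case against.** The best defence is that drug-related is loose wording for treatment-related. Outcome measures uses the latter term for the endpoint that this test serves, and Interventions describes the dressing as part of what patients are treated with. The silver-allergy exclusion shows that the authors had dressing reactions in mind. This stands as a plausible account of intent, though it fits the silver dressing better than the plain polyester one. It does not remove the conflict, because the protocol never says that dressings count.

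Stronger readings are tempting and should be resisted:

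- *The test cannot see dressing reactions.* The text is undefined, not explicit. A reaction at an injected lesion could be recorded as drug-related by an assessor who does not know that a dressing was worn. The test may exclude such events; it need not.
- *Drug-attributed events must be equal across arms by design.* A dressing could alter local reactions at an injection site, so they may differ.
- *Causality is decided by staff who know the arm.* Nothing says so. Follow up puts a blinded assessor at the visits, and the person who decides relatedness is simply not named.
- *The trial will fail its safety objective.* All events are recorded, and nothing bars reporting them.

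It is also fair to say that the detail of safety definitions is often left to an analysis plan. Here, however, the protocol states a rule, and that rule conflicts with its own objective.

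**Conclusion.** The concern holds as a conflict of scope. The objective, the endpoint and the test define three different sets of adverse events. The tested set is the narrowest and is framed around the component that all arms share. Taken literally it may drop reactions attributed to the dressing, and the blinded assessor could not reliably make the distinction it requires.

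The size is uncertain. Full filtering would leave a 1.3% to 2.5% chance of a significant result whatever the dressing did. An any-cause comparison would have about 4% to 73%, depending on the dressing reaction rate and the number of patients. These figures rest on assumed rates, independent patients and pairwise testing. They show the direction of the problem and also that the corrected test would be weak for uncommon reactions.

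This is a secondary safety analysis. The primary endpoint and the sample size are untouched. The correction should be made because it is nearly free and brings the test into line with the stated objective.

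**What to change.** In Statistical methods, keep relapse in its own sentence and replace the adverse event part with wording such as: the proportion of patients with at least one adverse event of any cause during the study period will be compared across the three groups by Fisher's exact test.

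Report events attributed to the drug or to a dressing descriptively by arm, with a statement of who makes the attribution and whether that person knows the allocation. Local events at treated sites may be tabulated in the same way; this is optional.

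Use the same scope in both statements of the Secondary objectives and in Outcome measures, and count patients, not lesions.

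The cost is wording only, since adverse events are already recorded at every visit without a filter. The drawback is that an any-cause comparison takes in background events and so dilutes the contrast. The descriptive table of attributed events is there to offset this. Any power quoted for the comparison should be given as a range on stated assumptions.
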